## **Data Handling**

Each study population comprises multiple datasets that will undergo a systematic cleaning process based on pre-defined eligibility criteria, provider type, encounter type, department id, and date.

Datasets will be merged using Encounter ID, Patient ID, and a unique identifier generated by combining Patient ID and Date. This approach is necessary due to the varying ID structures across datasets; for instance, the demographic dataset includes only Patient ID, while other datasets contain both Patient ID and Encounter ID. In cases where Encounter ID is missing, the combination of Patient ID and Date will be utilized to maximize the use of available data.

To ensure data integrity, a manual examination will be conducted to address other data-related issues, including duplication and inconsistencies. Intermediate checks will involve assessing missing values and verifying data consistency, while final checks will evaluate the completeness and accuracy of the datasets. We will also document all data handling procedures to ensure transparency and reproducibility.

### **Primary and Secondary Analyses**

The intervention consists of a real-time alert in the electronic medical record that will notify healthcare personnel when a non-pregnant woman aged 18-24 is eligible for chlamydia screening, defined as having no test order in the past year.

- **Primary Analysis:** The primary outcome will be the number of chlamydia screening orders placed during encounters. We will compare test order rates between intervention and control groups in primary care and obstetrics/gynecology practices.
- **Secondary Analysis:** The secondary analysis will evaluate the impact of the electronic alert on screening rates during reproductive health visits versus other visit types.

For each primary and secondary outcome, we will report the intervention effect as an odds ratio with a 95% confidence interval and P value (see Statistical Methods).

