## **2. Study Objectives**

The hypothesis of this study is that proportion of women ordered chlamydia screening will be higher in practices randomized to an electronic alert directed at medical assistants during rooming in of patients for their office visit than in practices without the electronic alert. Our primary objective is to compare the test order rates for *C. trachomatis* between practices randomized to the electronic alert compared to practices operating under routine care, separately for primary care practices and OBGYN practices. The secondary outcome will be to determine the test order rate in visits for reproductive care compared to visits for other medical reasons.

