## **7. Data Collection and Management**

The research informatics team at UPMC (CARE, see below) will capture pertinent clinical data in EMR for women attending in both the intervention and control practices. They will provide demographic and clinical information for data analyses that will include age, race, reason for visit, clinical services performed, chlamydia and gonorrhea test orders, and test results (if test results are available). All data will be de-identified prior to transfer to the investigators and to the CDC for data analyses.

The Center for Assistance in Research using eRecord (CARE) provides facilitated managed, compliant and secure access to the UPMC Electronic Health Record for researchers. CARE utilizes the EMRs and databases in use by UPMC. EMRs are currently deployed in both inpatient and outpatient clinics throughout the health system and provide a wealth of information for investigators. EpicCare is the EMR product in use in ambulatory clinics and outpatient offices affiliated with UPMC. The data contained in the EMRs are maintained behind a secure firewall on servers within the UPMC data center.

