### **Statistical Methods**

In this study, we will employ the following statistical methods to analyze the impact of a real-time alert system on chlamydia screening orders:

- **Baseline Characteristics:** Baseline characteristics will be summarized by study arm within each cohort (primary care and obstetrics/gynecology). Between-arm differences may be evaluated using 2-sided hypothesis tests ( $\alpha = 0.05$ ); however, P values will not be presented in Table 1. As a supplementary, sample size-independent measure,

standardized mean differences (SMDs) may also be calculated to aid interpretation of the magnitude of baseline differences and, if used, will be summarized briefly in the text.

- **Constrained Difference-in-Differences Mixed Effects Logistic Regression (Primary Approach):** We will estimate the intervention effect using a constrained difference-in-differences mixed-effects logistic regression model with a logit link. The model will include fixed effects for time period and the time-by-intervention interaction to compare pre-to-post changes between intervention and control practices. Random intercepts for practice (cluster) and patient will be included to account for within-cluster correlation and repeated encounters within patients. Models will be fit separately for primary care and obstetrics/gynecology practices. We will also report the intraclass correlation coefficient (ICC) to quantify the within-cluster correlation in the outcome, which is relevant for interpreting clustering and the precision of cluster-randomized estimates.
- **Small-Sample Inference for Cluster Randomized Designs:** Because the number of randomized clusters is fewer than 50, 95% confidence intervals and P values will be constructed using a t distribution with degrees of freedom (df) equal to  $K - p$ , where  $K$  is the number of clusters, and  $p$  is the number of cluster-level covariates included in the model.

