## **Significance Levels**

The familywise significance level will be set at  $\alpha = 0.05$  (2-sided). Because the primary endpoint will be evaluated in 2 parallel cohorts (primary care and obstetrics/gynecology practices), we will apply a Bonferroni correction, using  $\alpha = 0.025$  per cohort-specific primary comparison. For secondary outcomes, hypothesis tests will be interpreted using a 2-sided significance threshold of  $\alpha = 0.05$  unless otherwise specified.

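### The protocol and the SAP define the secondary question differently, and the only stated model does not estimate or test a difference in alert effect by visit type

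*Combined protocol and SAP*

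**What the plan says.** Protocol section 2 (Study Objectives): "The secondary outcome will be to determine the test order rate in visits for reproductive care compared to visits for other medical reasons". Neither the study arm nor the alert appears in that sentence.

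SAP, Primary and Secondary Analyses: "The secondary analysis will evaluate the impact of the electronic alert on screening rates during reproductive health visits versus other visit types". Here the alert is the subject and visit type is the modifier.

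SAP, Statistical Methods, gives one model: "The model will include fixed effects for time period and the time-by-intervention interaction to compare pre-to-post changes between intervention and control practices". It adds random intercepts for practice and patient, and the only split is by cohort: "Models will be fit separately for primary care and obstetrics/gynecology practices". No visit-type term and no fit within visit type is mentioned.

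For output, Primary and Secondary Analyses points back to that model: "For each primary and secondary outcome, we will report the intervention effect as an odds ratio with a 95% confidence interval and P value". Significance Levels sets the threshold for secondary tests at 0.05, two-sided, unless otherwise specified.

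Protocol section 7 lists among the data to be extracted "reason for visit, clinical services performed, chlamydia and gonorrhea test orders". Neither document says how a visit is classed as reproductive.

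**The concern.** Both sentences are current text and they describe different quantities. The protocol's contrast compares kinds of visit. Visit type is not randomised, and order rates would be expected to differ by reason for attending whether or not an alert exists. The SAP's contrast is effect modification, that is, a difference in the randomised effect between two kinds of visit. Two analysts working faithfully from the two sections could report different numbers as the secondary result.

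The SAP's version also has no matching estimator. A model with period and period-by-intervention terms gives one alert effect per cohort, averaged over visit types. If the team fits it separately in reproductive and other visits, the output is two odds ratios with intervals and P values and no planned contrast between them. A significant result in one and a non-significant result in the other could then be read as evidence that the alert works differently, which that pattern alone does not show. This is the trial's only named secondary question.

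**Working it through.** **Step 1. Are the two definitions the same quantity, and does the stated model answer the SAP's?** From protocol section 8: arm rates of 30% and 35%. Assumed, because the documents give no figures: half of visits are reproductive, and control order rates are 40% (reproductive) and 20% (other), averaging 30%. Post-period only, no clustering.

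Three scenarios share the same arm totals:

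| Alert effect | Alert-arm rate, reproductive / other | Alert OR, reproductive / other | Ratio of ORs (SAP question) | OR without visit-type term | Reproductive vs other OR, arms pooled (protocol question) |
|---|---|---|---|---|---|
| Equal OR | 45.9% / 24.1% | 1.27 / 1.27 | 1.00 | 1.256 | 2.66 |
| Reproductive only | 50% / 20% | 1.50 / 1.00 | 1.50 | 1.256 | 3.27 |
| Other only | 40% / 30% | 1.00 / 1.71 | 0.58 | 1.256 | 2.00 |

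- OR without visit-type term: (0.35/0.65)/(0.30/0.70) = 1.256 in every row.
- Ratio of ORs: 1.50/1.00 = 1.50 in the second row and 1.00/1.71 = 0.58 in the third.
- Protocol contrast, second row: pooled rates are (40% + 50%)/2 = 45% and 20%, so (0.45/0.55)/(0.20/0.80) = 3.27.

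The model without visit type returns the same odds ratio for three different answers to the SAP's question. The protocol's contrast is 2.66 even when the alert effect does not differ at all. With a pre-period and random intercepts the exact values would move, but a model without visit type would still contain no parameter for the contrast.

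**Step 2. What if the model is fitted within each visit type?** The plan states no figure for the secondary question. The 90% power used here is that of protocol section 8, which I reproduced first:

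- Pooled-variance formula: n = [1.96·√(2·0.325·0.675) + 1.2816·√(0.30·0.70 + 0.35·0.65)]²/0.05² = 1842.
- With continuity correction: (1842/4)·[1 + √(1 + 4/(1842·0.05))]² = 1882 per arm, as stated.

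This is a patient-level calculation with no design effect. Now take equal true effects, independent subgroup estimates and no clustering. The overall expected z is 1.96 + 1.2816 = 3.24. A subgroup with share f has expected z = 3.24·√f and power p = Φ(3.24·√f − 1.96). The chance that exactly one subgroup is significant is p₁(1 − p₂) + p₂(1 − p₁).

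- 50/50: p = 0.630 each; 2·0.630·0.370 = 0.47.
- 30/70: p = 0.427 and 0.774; 0.427·0.226 + 0.774·0.573 = 0.54.
- 20/80: p = 0.305 and 0.826; 0.305·0.174 + 0.826·0.695 = 0.63.

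On the same assumptions the interaction's standard error is √(1/f + 1/(1 − f)) times that of the overall effect: 2.0 at 50/50 and 2.5 at 20/80.

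**Step 3. How much does clustering matter?** The same practices supply both visit types, so shared practice effects correlate the two estimates and partly cancel from their difference. I used a linear analogue of the SAP model. Its settings are assumptions and not from the documents: 10 practices per arm, equal periods, 100 to 200 encounters per practice-period, ICC 0.01 to 0.10, patient effect ignored, both subgroup effects from one joint fit, 90% overall power.

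- Constant practice intercept, 50/50: exactly one significant in 30–36%; SE ratio 1.4–1.6.
- Constant practice intercept, 20/80: 48–55%; SE ratio 1.8–2.0.
- Practice-by-period variation added (between-period correlation 0.8), 50/50: 10–34%; SE ratio 0.65–1.5.
- ICC 0 returns the Step 2 figures.

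Visit-type effects that vary between practices would move these figures partly back towards Step 2.

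**The case against.** The strongest reply is that this is underspecification and not a wrong analysis. Protocol section 9 hands the analysis to the SAP, and the SAP ties the secondary question to the alert, so the looser protocol sentence may have no practical effect. The model is labelled the primary approach and need not list every secondary term. In this SAP the primary odds ratio is already an exponentiated interaction coefficient, so a three-way term would also be reported as an odds ratio with an interval and P value, which fits the promised output.

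Much of this stands, and it rules out several stronger readings:

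- A reader might infer that the SAP prescribes comparing two subgroup P values. It does not; it states no fit by visit type at all.
- A reader might infer that the planned odds ratios could show nothing about visit type. Two stratum odds ratios with confidence intervals would allow an informal comparison.
- A reader might take 47–63% as the error rate to expect here, or 2.0 to 2.5 as the interaction's relative standard error. Both are zero-ICC figures with independent subgroups. Step 3 shows that they can be much lower.
- A reader might infer that a non-randomised difference will be published as the trial result. That assumes the team follows section 2 over the SAP.

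What the reply does not remove is the text itself. Two current sections name different quantities, and no section specifies the contrast that the SAP asks for. A three-way term fits the SAP's wording, but the SAP does not state one.

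**Conclusion.** The point holds as a mismatch of definitions together with an unspecified contrast. The protocol's secondary outcome is a non-randomised comparison of visit types, the SAP's is a difference in alert effect, and the stated model as written does not estimate or test the latter. These conclusions rest on the text alone and need no numerical assumption.

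The possible misreading of one significant and one non-significant odds ratio is a consequence of having no planned contrast, and its frequency is not known for this trial. The range of about 47% to 63% is illustrative and rests on equal true effects, independence, 90% overall power, no clustering and assumed visit splits. The documents give neither the visit split nor an ICC. The interaction may be imprecise, but by how much is not established.

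The change should be made before analysis. It affects the secondary result only; the primary analysis is untouched.

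**What to change.** Align protocol section 2 with the SAP, so that the secondary objective in both is the difference in alert effect between reproductive and other visits.

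For each cohort, extend the SAP model with visit type, visit type by period, and period by intervention by visit type. This keeps the constraint of no baseline arm difference within each visit type. Add a practice-level random effect for visit type where it can be estimated, because the three-way test can be anti-conservative if practices differ in their visit-type contrast. State how the K − p degrees of freedom rule applies to this term.

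Report the ratio of odds ratios with its 95% CI and P value, at the 0.05 level already set for secondary tests, as the secondary result. Beside it give the alert odds ratio and CI within each visit type. Report raw order rates by visit type and arm as description only.

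Classify visit type from the reason for visit that section 7 already collects, by a rule fixed before analysis. Do not classify from services performed or orders placed, which the alert can affect.

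The cost is a wording change in both documents, one classification rule and one extra model per cohort, with no new data. The downside is that the interaction may be imprecise, and the plan should say so.

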## **Statistical Software**

All analyses will be conducted using R (version 4.4; R Foundation for Statistical Computing, Vienna, Austria), with appropriate packages as needed.

## **Significance Levels**

The familywise significance level will be set at  $\alpha = 0.05$  (2-sided). Because the primary endpoint will be evaluated in 2 parallel cohorts (primary care and obstetrics/gynecology practices), we will apply a Bonferroni correction, using  $\alpha = 0.025$  per cohort-specific primary comparison. For secondary outcomes, hypothesis tests will be interpreted using a 2-sided significance threshold of  $\alpha = 0.05$  unless otherwise specified.

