## **8. Sample Size Calculation**

Assuming that the screening rate in the usual care group is 30% and in the opt-out group it will be 35%, a study recruiting 1882 patients in the usual care group and 1882 patients in the opt-out group will result in 90% power to detect a significant difference in the proportion of women screened for chlamydia at a two sided .05 significance level. As such we propose to recruit at least 2000 patients in the opt-out group and 2000 patients in the usual care group.

If the baseline screening is closer to the 2011-2012 average commercial (non-Medicaid) screening rate of sexually active women (40% in 16-20 year olds and 47% in 21-24 year olds) we would need to enroll 898 women ages 16-20 and 228 women ages 21-24 in order to demonstrate a 20% increase in screening at 90% power. The proposed study would provide enough power to examine both of these age groups.

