## **STOP STDs Statistical Analysis Plan (SAP)**

### **Randomization**

The primary care and obstetrics/gynecology practices were each randomized separately in a 1:1 ratio into intervention (alert) or control groups. Randomization was accomplished in the primary care practices by stratifying the practices according to urbanicity of the county where the practice was located (US Department of Agriculture Rural Urban Continuity Code (RUCC) = 1 versus  $\text{RUCC} \neq 1$ ) and by stratifying according to the percentage of the practice patient population of eligible women who were African-American (above the median for African-American women versus below the median for African-American women). Practices in each of the resulting four stratification groups were randomized using a random number generator to be intervention or control. In obstetrics/gynecology practices, randomization was done by stratifying on the basis of the percentage of the practice patient who were African-American only, due to all but 1 of the obstetrics/gynecology practices being in  $\text{RUCC} = 1$ .

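### The two cohort-specific primary tests use a plain Bonferroni split; Holm's step-down rule holds the same familywise 0.05, needs no added assumption, and gives more power.

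*Combined protocol and SAP*

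**What the plan says.** The SAP's Significance Levels section gives the error target: "The familywise significance level will be set at $\alpha = 0.05$ (2-sided"). For the two primary tests it then says: "Because the primary endpoint will be evaluated in 2 parallel cohorts (primary care and obstetrics/gynecology practices), we will apply a Bonferroni correction", with 0.025 for each cohort's comparison. Secondary outcomes are tested at 0.05. No step-down, Hochberg or alpha-recycling rule appears in either the protocol or the SAP.

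There are exactly two primary P values. Statistical Methods in the SAP says "Models will be fit separately for primary care and obstetrics/gynecology practices", and the Randomization section says "The primary care and obstetrics/gynecology practices were each randomized separately in a 1:1 ratio". Protocol section 2 (Study Objectives) also poses the comparison separately for each type of practice, so either cohort can succeed alone.

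Protocol section 8 (Sample Size Calculation) gives one calculation: 30% versus 35%, 1882 patients per group, 90% power, two-sided 0.05. It does not use the 0.025 level of the SAP.

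**The concern.** Under the plan each cohort must reach 0.025 on its own. Suppose one cohort gives P = 0.01 and the other P = 0.04. The plan must call the second cohort negative. Holm declares both significant, and the familywise error rate is still at most 0.05. The plan therefore uses a rule that never rejects more than the alternative and sometimes rejects less, with no gain against its stated error target.

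What is at stake is a positive conclusion in one of the trial's two stated questions, whenever one P value is at or below 0.025 and the other lies between 0.025 and 0.05.

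**Working it through.** **1. The plan's own figures.** The split adds up: 0.025 + 0.025 = 0.05. The sample size also reproduces. For 30% versus 35%, two-sided 0.05 and 90% power, the usual two-proportion formula gives 1842 per group without continuity correction and 1882 with it, which is the protocol's figure.

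**2. Validity of Holm.** Order the two P values. If the smaller is above 0.025, stop. If not, reject it and test the larger at 0.05.
- Both nulls true: a false claim needs the smaller P value to be ≤ 0.025. The probability is at most 0.025 + 0.025 = 0.05 under any dependence, and 1 − (1 − 0.025)² = 0.0494 if the cohorts are independent. This is identical to Bonferroni.
- One null true: a false claim needs that cohort's P value to be ≤ 0.05, so the probability is at most 0.05.

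Simulation with 2 million draws at correlations −0.5, 0, 0.5 and 0.9 gave a familywise error of at most 0.0495 under Holm.

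**3. Power formulas.** Let a₁, a₂ be the cohorts' power at 0.025 and b₁, b₂ their power at 0.05, with independent cohorts.
- Bonferroni: a₁ for cohort 1; a₁a₂ for both.
- Holm: a₁ + (b₁ − a₁)a₂ for cohort 1; a₁a₂ + (b₁ − a₁)a₂ + (b₂ − a₂)a₁ for both.
- At least one success: 1 − (1 − a₁)(1 − a₂) under either rule.

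**4. Results under a normal approximation.** The power levels are assumptions.

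| Scenario | a | b | Per cohort, Bonferroni → Holm | Both, Bonferroni → Holm |
|---|---|---|---|---|
| Each cohort 90% at 0.05 | 0.841 | 0.900 | 84.1% → 89.1% | 70.8% → 80.7% |
| Each cohort 80% at 0.025 | 0.800 | 0.869 | 80.0% → 85.5% | 64.0% → 75.1% |
| 80% and 50% at 0.025 | 0.800; 0.500 | 0.869; 0.611 | 80.0% → 83.5%; 50.0% → 58.9% | 40.0% → 52.3% |

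For the first row: 0.841 + (0.900 − 0.841) × 0.841 = 0.891.

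**5. With t tests.** The SAP says there are fewer than 50 clusters and uses K − p degrees of freedom, but gives no K. Assume K = 12, 20 or 30 practices per cohort, K − 2 degrees of freedom, and 90% power at 0.05. Per-cohort power then goes from 81.5%, 82.7% and 83.3% to 88.4%, 88.7% and 88.9%.

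**6. With the protocol's sample size.** Assume that it applies to each cohort, without clustering.

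| Per arm | Power at 0.05 | Per cohort, Bonferroni → Holm | Both, Bonferroni → Holm |
|---|---|---|---|
| 1882 | 90.6% | 85.0% → 89.8% | 72.2% → 81.8% |
| 2000 | 92.2% | 87.2% → 91.6% | 76.0% → 84.7% |

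Reaching 90% power at a fixed 0.025 would take 2176 per arm (no continuity correction).

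**7. With clustering.** The documents give no ICC or cluster sizes for planning. At 2000 per arm in each cohort:

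| Assumed design effect | Per cohort, Bonferroni → Holm | Both, Bonferroni → Holm |
|---|---|---|
| 2 | 55.8% → 61.8% | 31.1% → 43.1% |
| 3 | 38.5% → 42.8% | 14.8% → 23.3% |
| 5 | 23.2% → 25.4% | 5.4% → 9.7% |
| 10 | 12.0% → 12.8% | 1.4% → 3.0% |

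**The case against.** The strongest reply is that nothing in the plan is wrong. Bonferroni is valid, the tests are counted correctly, and the level of each is stated. That stands: this point concerns efficiency only.

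The second reply is that Holm is not free within a single cohort. If the alert works in one cohort and does nothing in the other, the chance of a false claim in the null cohort is 0.025 under Bonferroni. Under Holm, in the first scenario, it is 0.025 + 0.025 × 0.841 = 0.046. A sponsor that wants a fixed 0.025 in each cohort for its own sake would have a reason to keep the split. But the SAP's stated target is the familywise 0.05, and 0.046 is within it.

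The third reply concerns size. The protocol's sample size is not given per cohort and makes no allowance for clustering, so 90% per cohort may be optimistic. With little power the first step seldom succeeds, and Holm then adds little. If the other cohort has no effect, the gain is about 0.1 percentage point: (0.922 − 0.872) × 0.025 = 0.0012. The chance of at least one success is unchanged. All of this limits the gain, but none of it is a loss.

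The fourth reply is that Bonferroni has simple matching 97.5% intervals and Holm does not. That is true, but the SAP already plans 95% intervals beside tests at 0.025, so little is lost. With the odds ratio, interval and P value reported for both cohorts, the evidence is visible under either rule; what changes is the formal conclusion.

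**Conclusion.** The concern holds. At the SAP's own familywise two-sided 0.05, Holm rejects everything Bonferroni rejects, sometimes more, and needs no assumption about dependence. If both cohorts carry real effects at the protocol's 90% planning level, the gain is about 5 percentage points per cohort and 10 points for success in both. Those sizes assume independent cohorts and the stated power in each; the validity of Holm does not. Holm recovers most, but not all, of what the split costs against an unadjusted 0.05 (89.8% against 90.6% at 1882 per arm). The change is worth making because it costs almost nothing, although the present rule is valid.

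**What to change.** Replace the Bonferroni sentence in Significance Levels with wording such as: *The two cohort-specific primary P values will be ordered. If the smaller is at most 0.025, that cohort is declared significant and the other is tested at 0.05. If the smaller exceeds 0.025, neither is declared significant (Holm). Holm-adjusted P values will be reported, and claims of significance will rest on them.* The adjusted values are twice the smaller P value, and the larger of that figure and the larger P value; with 0.01 and 0.04 they are 0.02 and 0.04.

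The SAP should also say that confidence intervals stay at one fixed level and that decisions come from the adjusted P values, because the interval level matching the second step depends on the other cohort's result.

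The cost is a few lines of SAP text, with no change to data, models or recruitment. The change must be made and dated before any comparison of outcomes by arm is seen. The SAP describes randomization as already done, and the documents do not show whether outcomes have been examined. If they have, the Bonferroni rule should stand for the primary claims.
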